**Fig. 1 Fig1:**
[figure not shown]
Prospective, observational, randomized study. Patients will enter the trial after completion the screening phase. Only patients aged ≥ 65 years and whose resulted as fragile using G8 screening tool with a score ≤ 14/17, will be randomized into 2 arms; Arm A: will be evaluated by Comprehensive Geriatric Assessment (CGA); Arm B: Control group. Both arms will be evaluated for their quality of life using EORTC – QLQ-C30 questionnaire, aiming to develop an accurate index for elderly patients with onco-hematological tumors using the CGA as primary study endpoint

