### Statistical design

The sample size was estimated by a two-tailed t-test (alpha = 0. 05, power = 0. 8 and an effect size Cohen (ES) equal to 0. 5) for a minimum clinically relevant difference of 10 points (SD = 20) on the global EORTC QLQ C30 Quality of Life scale. The planned sample size is 144 patients (72 per arm), considering a 10 % loss at follow-up. The primary endpoint will be evaluated on the ITT population. Baseline data will be summarized in terms of mean, standard deviation, median, I and III quartile, for continuous variables, and percentages for categorical variables. A test for the difference between two queued averages will be applied when comparing the total score for QoL. A level of significance of 5 % will be considered statistically significant. The study is expected to enroll about 144 patients with solid tumor neoplasms or hematological malignancies candidate to a first line treatment for advanced disease.

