### Study procedures

Comprehensive Geriatric Assessment (CGA): in arm A, patients receive a dedicated geriatric examination (60–90 min), administered by a dedicated geriatrician, and are classified according to CGA results and the Rockwood Frailty Index (RFI) as “frail” (RFI > 0.25), “unfit/prefrail” (0.08 > RFI < 0.25) or “fit” (< 0.08) [19].

The CGA includes evaluation of cognitive status with the Mini Mental State Examination (MMSE), Clock drawing test (CDT), and Montreal Cognitive Assessment (MOCA) [20]; of psychosocial status by the means of Geriatric Depression Scale (GDS) and Social Vulnerability Index (SVI) [21]; of disability by Activities of Daily Living (ADL) and Instrumental Activities of Daily Living (IADL) [22, 23]; of nutritional status by Mini Nutritional Assessment (MNA) [24]; of comorbidities by Cumulative Illness Rating Scale for Geriatrics (CIRS-G) and of pharmacological impact by number of drugs [25]; of sarcopenia and physical performance by Hand Grip Strength, Timed Up and Go test, Tinetti Scale, and number of falls in last six months [26]. CGA is performed at baseline and every 6 months. If issues are found in the areas of fragility, mid-term evaluations are foreseen, as indicated by the geriatrician. CGA based interventions will cover nutritional imbalance, social issues including the availability of caregiver and psychological interventions by dedicated psyco-oncologists.

In both arms, QoL assessment by the standardized EORTC QLQ-C30 questionnaire is performed at baseline (before treatment start) and every 3 months. Disease evaluation is performed in both arms according to local clinical practice. Patients are observed for up to 12 months or until disease progression (Fig. 4).

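### The primary endpoint is worded inconsistently (QLQ-C30 quality of life, a global scale, a total score, a CGA index), and the one sized test is tied to no visit

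*Protocol article*

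**What the plan says.** All places are in the Protocol article.

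- **Objectives:** the primary endpoint is health-related quality of life by the QLQ-C30. No scale, visit or summary over visits is given.
- **Statistical design, sizing:** the trial is sized for a "minimum clinically relevant difference of 10 points (SD = 20) on the global EORTC QLQ C30 Quality of Life scale", with a two-sided t-test at 5%, 80% power and 10% loss, giving 72 per arm.
- **Statistical design, analysis:** "A test for the difference between two queued averages will be applied when comparing the total score for QoL". The level is 5%.
- **Fig. 1 legend:** the design is called "Prospective, observational, randomized study". After saying that both arms are assessed with the QLQ-C30, the legend continues "aiming to develop an accurate index for elderly patients with onco-hematological tumors using the CGA as primary study endpoint".
- **Study procedures:** "QoL assessment by the standardized EORTC QLQ-C30 questionnaire is performed at baseline (before treatment start) and every 3 months". Patients are followed for up to 12 months or until progression. The legends of Figs. 2 and 3 list M3, M6, M9, M12 and progression.
- **Fig. 4 legend:** arm B has no scheduled geriatric visit.

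**The concern.** A primary comparison needs one variable, at one time or as one defined summary, so that the sample size, the test and the significance level refer to the same thing. Here the variable has one name where the trial is sized and another where it is tested, and a figure legend gives the role of primary endpoint to something measured in one arm only. Neither the sizing nor the test is attached to one of the four post-baseline visits, and neither says whether the value or the change from baseline is compared.

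This leaves two things open. First, the power depends on which visit and which form of the endpoint is used, and later visits may hold fewer patients because observation can end at progression. Second, if the choice were made after seeing data by arm, the 5% level would no longer protect the result, and a positive finding would be open to the charge of selective reporting.

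**Working it through.** **1. The plan's own figure.** Inputs from Statistical design: difference 10, SD 20 (d = 10/20 = 0.5), two-sided 5%, power 80%, loss 10%.

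- Normal approximation: n = 2(1.96 + 0.8416)² / 0.5² = 62.8, so 63 per arm.
- t-test (noncentral t): 63.77, so 64 per arm.
- Allowance for loss: 64 / 0.90 = 71.1, so 72 per arm and 144 in total.

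The stated 144 is reproduced exactly. With 64 to 65 evaluable per arm the power is 80 to 81%.

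**2. Power by form of endpoint.** Assume that SD 20 is the SD of the value at a visit, that 65 per arm are evaluable, and that the true difference is 10 points throughout. The correlation ρ between measurements is assumed, since the document gives none.

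| Form | SD formula | ρ = 0.3 | ρ = 0.5 | ρ = 0.7 |
|---|---|---|---|---|
| Value at one visit | 20 | 81% | 81% | 81% |
| Change from baseline | 20√(2(1−ρ)) = 23.7, 20.0, 15.5 | 67% | 81% | 95% |
| Baseline-adjusted value | 20√(1−ρ²) = 19.1, 17.3, 14.3 | 84% | 90% | 98% |
| Mean of four visits | 20√((1+3ρ)/4) = 13.8, 15.8, 17.6 | 98% | 95% | 89% |

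The choice of form can lower or raise the power. Only change from baseline at low correlation falls below 80%.

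**3. Power by visit.** Evaluable per arm = 72(1 − loss), d = 0.5, value at that visit. The 10% is from the document; the other loss rates are assumed.

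| Loss | Evaluable per arm | Power |
|---|---|---|
| 10% | 64.8 | 81% |
| 20% | 57.6 | 76% |
| 30% | 50.4 | 70% |
| 40% | 43.2 | 63% |
| 50% | 36.0 | 55% |

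**4. False-positive risk if the visit stays open.** Suppose each of the four visits could be tested at 5% and any one of them claimed.

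- Independent visits: 1 − 0.95⁴ = 18.5%.
- Correlated visits: Z_k = √ρ·C + √(1−ρ)·E_k for k = 1 to 4, with C and E_k independent standard normal, and P(max|Z_k| > 1.96) from one million draws. The result is 15.6% at ρ = 0.5, 13.0% at 0.7 and 11.4% at 0.8 (17.4% at 0.3 and 9.4% at 0.9).

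**5. Formal testing of all four visits.** With Bonferroni (0.05/4 = 0.0125 each), 91 evaluable per arm are needed: 91/0.9 = 101.1, so 102 per arm or 204 in total. With 144, the power at any one visit would be about 62%. The planned size therefore fits one primary comparison.

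**6. The Fig. 1 endpoint.** Objectives makes QoL primary, while the legend gives that role to an index using the CGA. The CGA is done in arm A, and no geriatric visit is scheduled in arm B. A CGA index has no arm B value, so it cannot serve for the randomised comparison.

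**The case against.** - **Global and total may be one scale.** The two terms stand in the same paragraph, the English is rough, and no separate total score is defined anywhere. A reader might infer three incompatible endpoints, or that the 10 points and SD 20 belong to a different variable from the one tested. The document does not show this. The two terms are an ambiguity; the firm contradiction is between Objectives and the Fig. 1 legend.
- **The legend is a caption slip.** It also says that both arms are assessed with the QLQ-C30, and Study Design clearly describes 1:1 randomisation. A reader might infer from the word observational that the design itself is in doubt. It is not, and the word has no bearing on error or power. The statement about the primary endpoint still needs correcting.
- **One test is planned.** A reader might conclude that the type I error is not 5%, or add a second score and count eight tests. Statistical design speaks of a test in the singular, and a single pre-specified test has 5% error. The four-visit figures show what an open choice would permit. An eight-test figure would also need a second score that the document never defines.
- **The article is condensed.** The full protocol or the SAP may fix the visit, the form and the model. That is fair, and the silence on the visit alone would not carry the point. But this article states the sizing, the test and the level itself, gives the variable two names, and contradicts itself on the primary endpoint. An unseen document does not remove that.
- **The power is not groundless.** The test, scale, difference and SD are given, and 144 reproduces. This stands: what is missing is the link to a visit and a form.

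**Conclusion.** The point holds as an inconsistently fixed primary endpoint. The Fig. 1 legend contradicts Objectives, and it names a quantity that cannot be compared between arms. The sizing and analysis sentences use different names for the outcome, and neither is tied to a visit.

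The arithmetic behind 144 is right. The 80% is the power for the global scale, taken as a value at one visit with at most about 10% loss. It falls to about 70% at 30% loss and 55% at 50%, and for change from baseline it runs from 67% to 95% over correlations of 0.3 to 0.7. These loss rates and correlations are assumptions. So is the reading of SD 20 as the SD of a single value.

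The 11–16% false-positive risk (correlation 0.8–0.5, assumed) is a worst-case illustration of leaving the visit open. It does not describe the planned analysis.

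**What to change.** Before any comparison by arm:

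- Name one primary endpoint: the QLQ-C30 global QoL scale at one pre-specified visit, or one defined summary over visits, compared as arm A minus arm B at two-sided 5%. M6 is a reasonable example, because the first repeat CGA falls then, but the document does not dictate it. Check that 10% loss is plausible at the visit chosen.
- Preferably estimate the difference from a baseline-adjusted repeated-measures model that uses all visits.
- Use the same scale name in the sizing and analysis sentences of Statistical design, and make the other visits and scores secondary.
- In the Fig. 1 legend, describe the CGA index as an exploratory arm A analysis and remove the word observational.

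The cost is a change of wording in the protocol and analysis plan; N = 144 can stand. The sponsor gives up the freedom to headline another visit or score. Trial status reports 63 patients randomised out of the planned 144, so recruitment was still under way when the article was written.

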### Study Population

The ONCO-aging study was approved by the referral Ethical Committee (EC) of Maggiore della Carità Hospital, in Novara, IT, on December 18, 2019 (CE 230/19). Accrual in the ONCO-AGING trial started on January 14, 2020; study is actively recruiting. Main inclusion criteria are: age ≥ 65 years; diagnosis of advanced solid tumor or hematologic cancer at any stage, candidate to first line therapy with innovative target agents or combined RT and CT schedules; G8 score ≤ 14/17; signed IC. Patients with a life expectancy < 3 months are excluded.

### Study procedures

Comprehensive Geriatric Assessment (CGA): in arm A, patients receive a dedicated geriatric examination (60–90 min), administered by a dedicated geriatrician, and are classified according to CGA results and the Rockwood Frailty Index (RFI) as “frail” (RFI > 0.25), “unfit/prefrail” (0.08 > RFI < 0.25) or “fit” (< 0.08) [19].

The CGA includes evaluation of cognitive status with the Mini Mental State Examination (MMSE), Clock drawing test (CDT), and Montreal Cognitive Assessment (MOCA) [20]; of psychosocial status by the means of Geriatric Depression Scale (GDS) and Social Vulnerability Index (SVI) [21]; of disability by Activities of Daily Living (ADL) and Instrumental Activities of Daily Living (IADL) [22, 23]; of nutritional status by Mini Nutritional Assessment (MNA) [24]; of comorbidities by Cumulative Illness Rating Scale for Geriatrics (CIRS-G) and of pharmacological impact by number of drugs [25]; of sarcopenia and physical performance by Hand Grip Strength, Timed Up and Go test, Tinetti Scale, and number of falls in last six months [26]. CGA is performed at baseline and every 6 months. If issues are found in the areas of fragility, mid-term evaluations are foreseen, as indicated by the geriatrician. CGA based interventions will cover nutritional imbalance, social issues including the availability of caregiver and psychological interventions by dedicated psyco-oncologists.

In both arms, QoL assessment by the standardized EORTC QLQ-C30 questionnaire is performed at baseline (before treatment start) and every 3 months. Disease evaluation is performed in both arms according to local clinical practice. Patients are observed for up to 12 months or until disease progression (Fig. 4).

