Likewise, it can be speculated that the biological age measured by the CGA and expressed in terms of fitness, unfitness and frailty could be related to a progressive inefficiency of the immune system, that might be predominant in frail patients. This hypothesis derives from the observation that in patients with solid and hematological malignancies, CGA-defined frail patients seem not to benefit from potentially life-saving therapies compared with younger counterparts [20]. Many studies provided evidence that the unfavorable outcome of elderly patients is partly related to clinical and biological differences in the disease itself, such as a more aggressive phenotype, more frequent advanced stage and presence of symptomatic disease [30]. To clarify this aspect, we added a biological aspect in our study to evaluate the role of T cell senescence and MDSC in our cohort of frail patients and to investigate the possible relationship among age, immune senescence and frailty.

Our trial has some limitations. It is a monocentric exploratory study, with a limited number of patients with different solid and hematologic tumors. The different types of diseases that can be included usually have different timepoints for the radiological and clinical evaluations, but as a starting protocol, we decided to identify standard timepoints visits for geriatric and radiologic evaluations, according to local clinical practice and guidelines. On the other side, given the network organization of the “Rete Oncologica Piemontese”, where the University Hospital Maggiore della Carità in Novara, IT, is the second most important hub in the region, and therefore is allowed to prescribe innovative oncological treatments and to perform aggressive combination therapies with the association of RT and CT, the probability of poor compliance or drop out during follow up is minimal. This eventuality is also further reduced by the regular introduction of palliative simultaneous care in frail patients of any age, being our center an ESMO designated center for simultaneous care. The results of the ONCO-aging study, dedicated to the elderly patient population, will be used to define a global strategy within the “UPO AGING project”, to improve our aging-specific research with a multicenter study including a larger number of patients and a more selective division by cancer type and treatments.

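### Observation stops at disease progression, but the ITT quality-of-life comparison and its 10% loss allowance make no visible provision for patients who progress

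*Protocol article*

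**What the plan says.** All references are to the protocol article.

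- **End of observation (Study procedures):** "Patients are observed for up to 12 months or until disease progression". The sentence points to Fig. 4, the assessment-timepoint figure, whose caption includes the three-monthly QLQ-C30.
- **Questionnaire schedule (Objectives):** QLQ-C30 at baseline and three-monthly through treatment and follow-up. This section states no stop at progression.
- **Schedule figures (captions of Figs 2 and 3):** the abbreviations cover months 3, 6, 9 and 12 and a time point at progression. The figures are not available, so it is unknown whether a questionnaire is given at that time point.
- **Analysis set (Statistical design):** "The primary endpoint will be evaluated on the ITT population". The comparison is of two averages. No primary visit is named.
- **Sample size (Statistical design):** "The planned sample size is 144 patients (72 per arm), considering a 10 % loss at follow-up".
- **Population (Study Population):** G8 of 14 or less, first-line treatment, advanced solid tumour or haematological cancer at any stage.
- **Expected loss (Discussion):** "the probability of poor compliance or drop out during follow up is minimal". The reasons given are the regional oncology network and simultaneous palliative care. Both concern adherence and dropout, not the planned end of observation.

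**The concern.** Progression is an outcome of the disease and its treatment. If it also ends quality-of-life collection, follow-up of the primary endpoint is cut by an event that occurs after randomisation and is likely to be related to the endpoint. Two things are at stake.

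1. **Completeness.** At a fixed later visit, patients who have progressed have no score. An ITT comparison there cannot rest on observed data from everyone randomised, and no analysis plan can recover scores that were never collected. The 10% allowance reads as ordinary loss to follow-up, with nothing visible for progression.
2. **Comparability.** The secondary objectives ask whether geriatric assessment changes treatment modification, adherence and patient outcome. If it changes progression, the patients still under observation at a visit are a differently selected group in each arm.

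**Working it through.** **Inputs from Statistical design.** Two-sided t-test, alpha 0.05, power 0.80, difference 10, SD 20, so d = 10/20 = 0.5; 72 per arm; 10% loss.

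**Inputs that are assumed.** The article gives no progression rate and no primary visit. I take exponential time to progression, no QLQ-C30 score at a fixed visit after progression, and no other loss.

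**Step 1: reproduce the plan's figure.** The noncentral-t calculation gives 63.8, so 64 evaluable per arm (power 0.801). Then 64/0.9 = 71.1, so 72 per arm and 144 in total. This matches the plan exactly.

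**Step 2: tolerance.** 80% power needs 64 of the 72, so the largest total loss is 1 − 64/72 = 11.1%.

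**Step 3: progression rate that the allowance implies.** Still under observation at month t: 0.5^(t/median). Setting this equal to 64/72 gives median = t × ln 2 / ln(72/64) = t × 0.6931/0.1178 = t × 5.885.

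| Visit | Median time to progression needed |
|---|---|
| M3 | 17.7 months |
| M6 | 35.3 months |
| M12 | 70.6 months |

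**Step 4: power under assumed medians.** Evaluable per arm = 72 × 0.5^(t/median); power from the same t-test.

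| Assumed median | M3 | M6 | M12 |
|---|---|---|---|
| 6 months | 50.9 per arm, 70% | 36.0, 55% | 18.0, 31% |
| 12 months | 60.5, 78% | 50.9, 70% | 36.0, 55% |
| 18 months | 64.1, 80% | 57.2, 75% | 45.4, 65% |
| 36 months | 68.0, 82% | 64.1, 80% | 57.2, 75% |

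A further 10% ordinary dropout would lower these. With a 12-month median they become 73%, 66% and 51%.

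**Step 5: when the arm contrast shifts.** Let a share p of an arm progress, with scores D points below those of its non-progressors. The mean among those still observed is the arm's full mean plus p × D. With a true difference of 10, the observed difference is 10 + pA × D − pB × D.

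- Equal progression (40% and 40%, D = 15): 10 + 6 − 6 = 10.0. No bias.
- Unequal progression (30% in arm A, 50% in arm B, D = 15): 10 + 4.5 − 7.5 = 7.0.

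These shares and D are illustrative assumptions.

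**The case against.** The strongest reply is that the document does not show how much quality-of-life data will be missing. The sample size is arithmetically correct. With no progression rate and no primary visit, any shortfall is conditional: at month 3 with a median of 18 months, power is still 80%. Objectives states no stop at progression, and the captions of Figs 2 and 3 leave room for a form at that time. How missing scores and deaths enter an ITT analysis is commonly left to the analysis plan, which is not shown.

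Most of this stands, and it rules out several stronger readings that a reader might infer.

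- **That the ITT analysis and 80% power cannot hold, or fail at every later visit.** This would need a progression rate and a primary visit, and the article gives neither.
- **That the randomised comparison is broken.** Step 5 shows no shift when progression and the progressors' deficit are equal across arms. Bias is a risk, not a demonstrated result.
- **That arm A's additional visits bring progression to light earlier.** Those visits are geriatric. Disease evaluation follows local practice in both arms.
- **That the Discussion contradicts the stopping rule.** It speaks of compliance and dropout, which is a different matter.

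The reply does not remove the point. The rule on observation is stated, not omitted. A form at progression would fall at a patient-specific time and would not supply the scheduled later scores. An analysis plan chooses how to handle data; it cannot bring back scores that the protocol does not collect.

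**Conclusion.** The point holds in this form. As Study procedures is worded, the primary endpoint is truncated at an outcome-related event, while Statistical design promises an ITT comparison with one 10% allowance that shows no provision for progression. The stated 144 and 80% are correct for their inputs. They carry through to the analysis only if total loss stays within 11.1%, which progression alone would exceed unless the median is about 18 months or more for month 3, 35 for month 6 or 71 for month 12.

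Under an assumed median of 6 to 12 months, power would be 70–78% at month 3, 55–70% at month 6 and 31–55% at month 12. These figures rest on exponential progression, no fixed-visit score after progression and no other loss. The effect is small or absent for an early visit with slow progression and large for a late visit with faster progression. Bias in the arm contrast is possible but depends on the arms differing in progression or in progressors' quality of life. The remedy is cheap enough to be worth making whichever case applies.

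**What to change.** 1. **Study procedures:** amend it, and reconcile it with Objectives and Statistical design, so that QLQ-C30 continues every 3 months to month 12 in all living randomised patients, regardless of progression or change of treatment. This alters data collection only, not clinical management.
2. **Statistical design:** name the primary visit. Either justify the loss allowance with an expected rate of progression and death, or restate the evaluable number and power at that visit.

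**Cost.** A short amendment, some added questionnaire burden and some missing forms after progression. The stated power may look less favourable. The change in collection needs no extra patients. Trial status reports 63 randomised, so at that point 144 − 63 = 81 planned patients were still to enter and would be covered from the start.
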